## Discussion

Here, a transdiagnostic, randomized, triple-blinded and sham-controlled neurotherapeutical brain stimulation trial is presented. From a translational perspective, this study promises high rewards to both: basic research in neuroscience as well as the fields of mental health. Regarding the former, by targeting one of its assumed neural substrates, we aim to add causal evidence to the involvement of the vmPFC in pathologies of emotion regulation. Further, we would establish a proof that anodal tDCS in combination with an optimized, multi-electrode montage can efficiently affect the targeted emotion regulation deficits via the modulation of one of its neural underpinning, namely the vmPFC. In contrast to previous tDCS studies, the simulation and modeling for the multi-electrode montages were based on MRI measures of both sexes, as well as in the optimal age range, adding specificity to the stimulation protocol. Electrical stimulation protocols aiming to target neural networks for e.g., changing the inhibitory/ excitatory balance in different brain regions [e.g., (125)] would be interesting for future endeavors, if evidence is repeatedly shown.

As the intervention has promising applications in psychiatry, it is important to point out, that the current project provides the first empirical, transdiagnostic tDCS therapy attempt in adolescents with depressive, anxiety and conduct disorders. With this approach, we aim to overcome disadvantages of standard therapies like side effects of or insufficient commitment to medication, long durations and related costs. Therefore, we developed a specific therapeutic brain stimulation procedure to achieve the greatest possible commitment on the patients' side, as well as the greatest possible neuromodulative effect. The training paradigm is built for the purpose to activate cognitive and emotional brain networks at the same time: brain regions involved in cognitive functioning (e.g., prefrontal areas), through the required actions during the tasks and at the same time brain regions involved in emotional functioning (limbic areas, e.g., amygdala), through the presentation of emotional stimuli. With this procedure, we expect to activate those brain areas through the training paradigm, which are simultaneously stimulated with tDCS.

Here, specific training effects have to be considered regarding potential biases in outcome measures. Both treatment groups undergo the described emotion regulation training, regardless of receiving real or sham stimulation. Therefore, we will not be able to reduce our results to the pure effect of the activation via tDCS since an induced modulatory training effect is actually desired. Moreover, the emotion regulation training itself might lead to improvements in both groups. If group differences in the improvements of the clinical outcome measures become insignificant, future research will be needed to differentiate between the training and stimulation influences. Only after this analysis, it is possible to clarify if only the developed emotion-cognition training procedure alone is sufficient for an effective training or if the brain stimulation further increases the therapeutic effect. In this case, also the influence of the engagement in the study *per se* would need to be investigated via a suitable control condition.

As the here presented clinical therapy trial not only includes three groups of patients and a novel brain stimulation procedure, but also pre- and post-measures on multiple levels (subjective psychological measures via self- and parent-rated questionnaires, behavioral and eye tracking tests, neuronal measures via MRI), inclusions of further diverging control groups would have gone beyond the scope of this single study.

Considering the developmental psychophysiological perspective, this project does not only highlight the treatment advantages of the excitability of the adolescent brain, it also takes the chance to possibly intervene early enough to hinder a further worsening of the clinical symptoms of depressive, anxiety or conduct disorders and the pathological manifestations in adulthood.

Utilizing a transdiagnostic approach for the treatment of emotion dysregulation as a common factor in anxiety, depressive and conduct disorders, this study is oriented toward a dimensional perspective on mental health as it was formalized in the Research Domain Criteria framework. If successful, this project will provide a non-invasive therapeutic option for the most prevalent psychiatric disorders in adolescents, with the possibility to transfer the protocol to related conditions in future studies.

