#### Stratification and Randomization

In a first step, participants displaying T-values of the FEEL-KJ Total score outside the clinical norm (T-value <40 or >60 in accordance with the transdiagnostic inclusion criterion of substantial emotion dysregulation) and in addition fulfilling the primary diagnosis of either a depressive, anxiety or conduct disorder, will be included in the study. Secondary diagnosis, especially comorbid disorders related to another subgroup of the current trial (e.g., primary diagnosis: depression and secondary diagnosis: anxiety) will be recorded and taken into consideration for the analysis. Age and sex will serve as stratification variables allocating 12 participants of each clinical group to one age block (age block1: 13 + 14 years; age block 2: 15 + 16 years; age block 3: 17 + 18 years) with half of the participants per age block being female and the other half male.

In a second step, a block randomization is performed: 50% of the participants of each block of each subgroup will be randomly allocated to the real or sham tDCS group, respectively (18 of 36 for each of the three clinical groups, female: male = 1:1). This results in 54 subjects per experimental condition (balanced related to clinical groups, age and sex; see Figure 1).

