#### Electrode Placement and Current Strength

Due to the inter-individual variability in the response to tDCS in adult studies (79, 80) as well as the specific features of the stimulation-generated electric fields' behavior in the youth population (81), a suggestion in the pediatric tDCS literature for simulation-based stimulation protocols has been brought up (53, 58). MRI-based finite-element models of the human head can assist parameter choice and dose individualization through the estimation of the spatial distribution and the magnitude of the electric fields (82). In children and adolescents, due to the fast changes in the anatomical characteristics (gray matter alterations, bone thickness, cortical-spinal fluid quantity), field magnitudes are usually 1.5–2 times higher than in the adults (83, 84).

Therefore, in this clinical trial, in an attempt to increase spatial precision in targeting the non-superficial cortical area of the vmPFC, an optimized high definition, multi-channel montage based on computational simulations, was chosen. For this reason, the optimization was conducted with the Stimweaver algorithm (Stimweaver montage optimization service from Neuroelectrics NE, Barcelona) to determine the positions of the computed 8 electrodes and required currents for the vmPFC (Figure 2). Based on two head models (male/female) generated from structural T1 images from adolescents within the same age range from a previous clinical trial ran by our research group, an optimized montage for female and male participants was calculated. For female participants anodal stimulation will include electrode positions FP1, FP2, FPz, and P08, while cathodal electrodes will be placed at electrode positions FC1, FC2, and Fz. For male participants anodal stimulation will include electrode positions FP1, FP2, and O1, while cathodal electrodes will be placed at electrode positions FC1, FC2, Fz, and F4. The maximal injected current into the brain at any given time will be below 2.00 mA and maximum current at any electrode is 1.00 mA. The electrodes used in this study are 1 cm radius Ag/AgCl cylindrical electrodes with conductive gel underneath (NG PiStim electrodes).

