#### Stimulation Protocol and Intervention Procedure

True anodal tDCS will be applied to the experimental group for 20 min. In the first minute, current will fade-in for 30 s to 2 mA and this current intensity will be maintained. In the 20th minute, tDCS will be reduced and fade-out in the last 30 s. During the sham stimulation in the control group, a fade-in phase for 30 s will be applied, followed by 15 s of 2 mA stimulation and then a fade-out phase for 30 s. Here, participants experience the typical skin sensation during the beginning and thereby will remain unaware of the real condition (85, 86).

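### The Discussion promises proof that tDCS works through the vmPFC, but real versus sham, both with the same training, can show only the added effect of the whole montage, and the stated imaging model does not fill the gap

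*Protocol article*

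**What the plan says.** Two statements about mechanism stand together in the first paragraph of the Discussion. The milder is an aim: "we aim to add causal evidence to the involvement of the vmPFC in pathologies of emotion regulation". The stronger is a conclusion announced in advance: "we would establish a proof that anodal tDCS in combination with an optimized, multi-electrode montage can efficiently affect the targeted emotion regulation deficits". The same sentence then gives the route, saying that the montage "can efficiently affect the targeted emotion regulation deficits via the modulation of one of its neural underpinning, namely the vmPFC".

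The design is set out elsewhere in the article:

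- **Arms.** Stratification and Randomization allocates participants 1:1 to real or sham stimulation: "This results in 54 subjects per experimental condition". There is no third arm.
- **Sham.** Stimulation Protocol and Intervention Procedure gives a 30 s fade-in, "followed by 15 s of 2 mA stimulation and then a fade-out phase for 30 s".
- **Training.** The Discussion states: "Both treatment groups undergo the described emotion regulation training, regardless of receiving real or sham stimulation".
- **Montage.** Electrode Placement and Current Strength gives females anodes at FP1, FP2, FPz and P08, and "cathodal electrodes will be placed at electrode positions FC1, FC2, and Fz". Males have anodes at FP1, FP2 and O1 and cathodes at FC1, FC2, Fz and F4.
- **Imaging.** Three task paradigms and a resting-state scan are acquired before and after the intervention. The fMRI paragraph of Statistical Analysis names diagnostic group and measurement time as group-model factors, with age and sex corrected for. It plans exploratory correlations with emotion regulation measures.

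Later in the Discussion, the article says of the shared training: "we will not be able to reduce our results to the pure effect of the activation via tDCS". It adds that further control groups were beyond the scope of the study.

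**The concern.** A sham-controlled trial identifies the effect of what differs between its arms. Here that is the full stimulation package, delivered alongside training. The vmPFC is the intended target of the package, but it is not the randomised factor. A claim that the effect runs through that region needs something more: an arm stimulating elsewhere, or at least evidence that real and sham stimulation change vmPFC activity differently and that this change goes with the clinical change.

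The article has no such arm, and the imaging model it states does not include the factor that would provide the second kind of evidence. If the trial is positive, its pre-stated interpretation would invite a report of a proven vmPFC mechanism on the strength of a questionnaire difference. That difference would fit a vmPFC mechanism, but it would equally fit action in any other region the current reaches.

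**Working it through.** The point concerns what the arms identify, so most of the check is reasoning from the text. The plan's one related figure is reproduced first, to show that it is not at issue.

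**1. The stated sample size.** Inputs from Sample Size Calculations: f = 0.25, α = 0.0167, power 0.80, two time points (m = 2), and the test-retest reliability 0.62 taken as the pre/post correlation ρ (an assumption). For the time-by-treatment interaction with two arms within one diagnostic group:

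- noncentrality λ = f² × N × m / (1 − ρ)
- at N = 36: λ = 0.0625 × 36 × 2 / 0.38 = 11.84, on 1 and 34 degrees of freedom, which gives power 0.816
- the smallest N reaching 0.80 is 35, or 36 for equal arms
- 3 × 36 = 108, as stated

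The figure reproduces. It concerns real versus sham, and nothing below alters it.

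**2. What each arm contains.** Write the mean FEEL-KJ change as:

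- sham arm = T + S
- real arm = T + S + M

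T is the change due to training, time and taking part. S is whatever expectation or brief current contributes under sham. M is what full stimulation adds when given with training. Sham current lasts 30 + 15 + 30 = 75 s per session including ramps, against 20 min (1,200 s) of real stimulation, so S need not be zero.

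- Real − sham = M.

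Training cancels because both arms have it. M is thus a valid estimate of the added effect of stimulation, on top of training and relative to this sham.

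**3. Why M does not identify the site.** M may combine an effect through the vmPFC with effects through other regions. There is one contrast and more than one unknown. Of the two arms, none delivers active stimulation aimed elsewhere. The electrode positions include frontal or frontocentral cathodes and a posterior anode in both sexes, and the montage differs by sex, so what was randomised is a sex-specific package.

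**4. Whether the imaging fills the gap.** What a mechanistic claim would need, against what Statistical Analysis states:

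| Needed | Stated |
|---|---|
| Real-versus-sham difference in pre-to-post change | Factors are diagnostic group and pre/post; stimulation condition is not named |
| A contrast in the vmPFC | Whole-brain group analyses |
| A link from vmPFC change to FEEL-KJ change | Exploratory correlations with impairment and emotion regulation indicators |

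The paragraph on the primary endpoint in the same section does name treatment condition; the fMRI paragraph does not. A pre/post effect pooled over arms cannot separate stimulation from training or the passage of time.

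**5. The later training paragraph.** It says that, if group differences are not significant, further research must settle whether training alone suffices or whether stimulation adds to it. By step 2, real versus sham is itself the test of whether stimulation adds to training. What the two arms cannot give is T alone, since the sham arm mixes it with S, or the effect of stimulation without training, which nobody receives.

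**The case against.** The strongest reply is that this is one over-confident sentence in a Discussion. The primary hypothesis, the primary outcome and the rmANOVA are all framed as real versus sham, and no decision rule turns a FEEL-KJ difference into a vmPFC conclusion. The stated objectives concern emotion regulation, symptoms, quality of life and functioning, not proof of mechanism. The montage was optimised by head-model simulation to reach the vmPFC. Pre/post imaging is planned, and a region-of-interest specification is the kind of detail an article leaves to a fuller plan.

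Much of this stands. The operative analysis is sound, the milder causal aim is modest, and the lack of a region-of-interest specification is not in itself a fault. Two things do not fall away. The sentence announces proof of a route, and simulated targeting is a reason to expect that route rather than evidence that it carried the effect. Also, the article does state its fMRI group factors, and the randomised factor is not among them.

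Four stronger readings are tempting, and the document does not support them:

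- **That the Discussion contradicts itself.** The training paragraph deals with training versus stimulation and says nothing about site. It sits uneasily with the word proof, no more. Its remark about not isolating tDCS is fairly read as saying that stimulation without training is never observed, which is true.
- **That a positive result would be treated as uninterpretable.** The call for further research is conditional on a null difference.
- **That the sham is inert.** It delivers a brief 2 mA current.
- **That counting electrodes away from the frontopolar sites measures the problem.** Scalp labels do not show where the field falls, and the field maps are not visible here. The article also speaks of eight computed electrodes but lists seven positions per sex (4 + 3 and 3 + 4), so the denominator is uncertain.

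**Conclusion.** The concern holds for what may be concluded. As designed, a positive FEEL-KJ difference would show that the sex-specific montage given with training does better than sham given with the same training. It would not establish that the effect runs through the vmPFC, and the imaging model as stated would not establish it either.

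The size is qualitative: no error rate, power figure or participant number changes, and the real-versus-sham test remains valid. What changes is the strength of the mechanistic conclusion, from proof to, at best, supportive evidence. This rests on reading the listed fMRI factors as the complete set. If a fuller plan already includes stimulation condition by time, the imaging part reduces to a correction of the article, while the point about the proof wording remains.

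**What to change.** 1. **Discussion, mechanism sentence.** Replace the proof claim with one matching the contrast, for example: a positive result would show that the sex-specific multi-electrode montage, given with the emotion-cognition training, improves FEEL-KJ scores more than sham with the same training; it would not by itself identify the region responsible. The aim of adding causal evidence may stay if it is tied to the supportive imaging analysis below.
2. **Statistical Analysis, fMRI paragraph.** Add stimulation condition and its interaction with time to the group model. Pre-specify, before unblinding, a vmPFC region of interest and the real-versus-sham contrast of pre-to-post change in it, for task and resting-state data, together with its relation to FEEL-KJ change. Label this supportive only: brain change is not itself randomised, and it is measured in the same post-intervention phase as the outcome.
3. **Discussion, training paragraph.** Clarify that real versus sham does test whether stimulation adds to training, and that what cannot be isolated is training alone or stimulation without training. Nothing else there needs changing.

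The cost is some rewording and a small analysis on scans already planned, with no new arm, participant or visit. The downside is a more modest mechanistic claim.

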## Trial Status

The described study started in November 2021; start of recruitment is planned for the beginning of 2022.

## Ethics Statement

The study was approved by the Ethics Committee of the Medical University of Vienna and the Austrian Agency for Health and Food Safety (AGES) and will be conducted according to the Declaration of Helsinki.

